#### Recruitment

Recruitment posters for this study will be prominently displayed at the outpatient clinic of Nanbu County People’s Hospital. In addition, the recruitment advertisement will be posted on the official WeChat public account of Nanbu County People’s Hospital to expand the audience and increase awareness. During the design phase of this trial, consultation will be conducted with representatives of patients with post-stroke pain to optimize the inclusion criteria.

#### Risk–benefit assessment

The potential benefits for participants and society include improved patient conditions and access to free medical care and condition assessments during the trial.

Risks to participants comprise treatment administration or withdrawal-related risks and the inherent risks of the disease. To protect participants’ health and interests during the trial, the researchers may discontinue the trial when necessary based on combination therapy/medication rules and discontinuation/withdrawal criteria, to protect participants’ health and interests.

#### Allocation of interventions

Participants will be randomized in a 1:1:1 ratio to the experimental group (YLDJJ acupuncture + rTMS), control group 1 (conventional acupuncture + rTMS), or control group 2 (sham acupuncture + rTMS). Block randomization with a fixed block size of 6 will be used via the blockrand package in R Statistical Software (v4.5.0). Each block will include 2 participants per group to maintain balanced assignments during recruitment. An independent statistician will manage the allocation sequence using sequentially numbered, opaque, sealed envelopes. Concealment will be maintained until intervention assignment to prevent disclosure to enrollment or assessment staff. After generating the randomization sequence, the independent clinical assessment center will directly notify the assigned intervention therapist of the randomization number and treatment group of each participant. Notifications will occur via encrypted text messages or secure WeChat, ensuring the integrity of allocation.

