### Study participants

This RCT will be conducted at Nanbu County People’s Hospital, following the Guidelines for the Diagnosis and Initial Management of Stroke and Transient Ischaemic Attack in Individuals Aged 16 Years and Over (33), and the Budapest Criteria for CRPS-I diagnosis (4). Specialist physicians will assess the eligibility of potential participants. Those who voluntarily participate will sign an informed consent form before enrollment.

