#### Sample size

Sample size was calculated using G*Power 3.1.9.7 software (40), based on the primary outcome measure of pain intensity assessed by the VAS. Key parameters were set as follows: a minimum clinically important difference (MCID) of 1.5 points on the VAS, a standard deviation (SD) of 1.8 points derived from pilot data, a two-tailed significance level (*α*) of 0.05, and a statistical power (1 − *β*) of 90%. For the three-arm parallel design, which is meant to be analyzed using one-way analysis of variance (ANOVA), an effect size (f) of 0.42 (classified as Cohen’s medium-to-large effect) was estimated (25). The initial calculation indicated a requirement of 33 participants per group. To account for a conservative dropout rate of 20%, resulting in a final allocation of 42 participants per group (total *N* = 126).

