#### Blinding and unblinding procedures

The rTMS devices used in both the experimental and control groups will be identical in appearance and operational sounds. Needles of the same specification (0.30 mm × 40 mm) will be used in the manual acupuncture group. Only the acupoints will differ between groups, thereby preserving blinding integrity.

Participants, outcome assessors, and statisticians will remain blinded to group assignment. Blinding will be ensured by using uniform rTMS devices and procedures across all groups, and acupuncture sessions will be conducted in private rooms to prevent participants from observing treatments administered to other groups. Practitioners performing YLDJJ or conventional acupuncture will not be blinded due to the technical requirements of the protocols. To minimize potential bias, they will adhere to standardized communication scripts, avoid discussing treatment details with participants, and will not participate in outcome assessments.

If unblinding becomes necessary after the participant’s withdrawal, the treating investigator will request allocation disclosure from the Clinical Evaluation Center. The reason for withdrawal, the revealed allocation, and the involved personnel will be documented. Full formal unblinding will be done by an independent statistician after trial completion, final follow-up, database lock, and preliminary analysis. Sealed envelopes will be employed, and the unblinding process will be thoroughly documented.

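### A fixed, published block size of 6 at one hospital leaves up to one allocation in five certain to anyone who knows the earlier allocations in the block

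*Protocol article*

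**What the plan says.** Under Allocation of interventions the article sets a 1:1:1 ratio and a constant block: "Block randomization with a fixed block size of 6 will be used via the blockrand package in R Statistical Software (v4.5.0"). It adds: "Each block will include 2 participants per group to maintain balanced assignments during recruitment". No stratification factor is named there. Under Study participants the site is a single one: "This RCT will be conducted at Nanbu County People’s Hospital". The text therefore describes one running list.

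The same allocation section gives the safeguards: an independent statistician, numbered opaque sealed envelopes, and concealment from enrolment and assessment staff up to the point of assignment. It also says that the therapist assigned to a participant is told that participant's randomization number and group through a secure channel.

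Under Blinding and unblinding procedures: "Practitioners performing YLDJJ or conventional acupuncture will not be blinded due to the technical requirements of the protocols". Those practitioners follow communication scripts and take no part in outcome assessment. The article does not state that they are kept apart from referral, screening or enrolment, or that the block size is withheld from site staff.

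**The concern.** Sealed envelopes hide the next assignment but do not prevent its deduction from past ones. When every block has the same known size and composition, the last places in a block can be worked out by anyone who has followed the earlier ones. If randomization numbers run in order, as numbered envelopes suggest, the number itself shows the place in the block and the message to the therapist supplies the arm.

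What is at stake is selection bias. If a coming assignment is known to someone who influences referral or enrolment, a patient can be brought forward, delayed or judged ineligible. Some eligibility criteria leave room for judgement, such as tolerability of both treatments. The primary outcome is self-reported pain on the VAS, so differences between arms in the kind of patient enrolled could carry into the result.

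**Working it through.** **Inputs from the article.** Three arms, 1:1:1; block size 6 with 2 per arm (Allocation of interventions); 33 per group before a 20% dropout allowance, 42 per group and 126 in total after it (Sample size).

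**The plan's own figures.** 33 / (1 − 0.20) = 41.25, rounded up to 42; 3 × 42 = 126; 126 / 6 = 21 complete blocks. These agree with each other.

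**Certain allocations, fixed block of 6.** The number of possible blocks is 6! / (2! × 2! × 2!) = 90. An allocation is certain when all places left in its block belong to one arm.

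- Places 1 to 4: never certain.
- Place 5: certain when the last two places belong to the same arm. There are 3 × 4! / (2! × 2!) = 18 such blocks, and 18/90 = 1/5.
- Place 6: always certain.

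The expected number per block is 1/5 + 1 = 1.2, and 1.2 / 6 = 20%. Over 21 blocks this is 21 × 1.2 = 25.2 of 126.

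**Partial knowledge.** At least one arm can be ruled out at place 3 in 20% of blocks (18/90), at place 4 in 60% (54/90), and at places 5 and 6 always.

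**Best guess.** An observer who always names the likeliest arm is right, at places 1 to 6, with probability 1/3, 2/5, 1/2, 8/15, 3/5 and 1. The sum is 101/30; divided by 6 this is 101/180 = 56.1%, against 33.3% by chance.

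**Varying block sizes.** These are simulations of 200 trials of 126 participants each. It is assumed that the sizes in a set are equally likely, and that the observer knows the set and every past allocation but not the order of the sizes.

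| Block sizes | Certain | Best guess |
|---|---|---|
| 6 fixed | 20% | 56% |
| 3, 6 | 9% | 58% |
| 3, 6, 9 | 4% | 55% |
| 6, 9 | 5% | 54% |
| 6, 9, 12 | 2% | 53% |

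Varying the size removes most of the certainty but hardly moves the best-guess rate. Including blocks of 3 works against the second measure: with 3 and 6 the rate rises slightly.

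**The case against.** The strongest reply is that the 20% belongs to an observer whom the article does not show to exist. A therapist is told about the participants assigned to that therapist. The article speaks of acupuncturists in the plural without giving their number, so knowing a whole block requires either one therapist treating everyone or several sharing information. Eligibility is assessed by specialist physicians, and allocation is concealed from enrolment staff until assignment. A reader might infer that therapists work alongside those who recruit, or that one allocation in five will in fact be foreseen at enrolment. The article says neither: it does not describe the two roles as overlapping, and it does not state their separation. For enrolling staff without the allocation history, nothing is predictable. This part of the reply stands, and it limits the point to exposure.

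It can also be said that the primary model adjusts for baseline VAS. That is true and would deal with selection on initial pain. It would not deal with selection on unmeasured prognosis.

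Finally, the allocation section contains no inconsistency: 6 is a multiple of 3 and fills 126 exactly. That is correct, and the point is an avoidable weakness in a stated design choice, not an error of arithmetic. An independent statistician and opaque envelopes do not answer it, because neither stops deduction from assignments already made.

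**Conclusion.** The point holds as a cheap improvement that should be made. With a fixed, published block of 6 in one list at one hospital, 20% of allocations (25.2 of 126 on average) are certain to an observer who knows all earlier allocations in the block. That figure is exact under its condition, and it is an upper bound on exposure, because it presumes that the knowledge is complete.

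It rests on three assumptions: that the list is unstratified, as the text describes; that one therapist treats all participants or several pool what they know; and, for bias to follow, that the knowledge reaches those who refer, screen or enrol. The article neither establishes nor excludes the last two. It therefore does not support the conclusion that concealment fails or that the result will be biased.

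**What to change.** In Allocation of interventions, replace the fixed block size with randomly varying sizes in multiples of 3, preferably without blocks of 3, for example 6 and 9, or 6, 9 and 12. The independent statistician should generate the list, and the sizes should not be disclosed to site staff until database lock. Add one sentence that treating acupuncturists take no part in referral, screening or enrolment; this addresses the route that varying sizes leave open.

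The expected gain is a fall in certain allocations from 20% to about 5% (6 and 9) or 2% (6, 9 and 12). No comparable gain should be claimed for guessing, which falls only from 56% to about 53–54%.

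The cost before the first allocation is a small change to the randomization code and a few words of protocol text. If allocation has begun, blocks not yet used can be regenerated and the change documented. The drawback is that arm sizes may differ by a few participants if recruitment stops mid-block.

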#### Blinding and unblinding procedures

The rTMS devices used in both the experimental and control groups will be identical in appearance and operational sounds. Needles of the same specification (0.30 mm × 40 mm) will be used in the manual acupuncture group. Only the acupoints will differ between groups, thereby preserving blinding integrity.

Participants, outcome assessors, and statisticians will remain blinded to group assignment. Blinding will be ensured by using uniform rTMS devices and procedures across all groups, and acupuncture sessions will be conducted in private rooms to prevent participants from observing treatments administered to other groups. Practitioners performing YLDJJ or conventional acupuncture will not be blinded due to the technical requirements of the protocols. To minimize potential bias, they will adhere to standardized communication scripts, avoid discussing treatment details with participants, and will not participate in outcome assessments.

If unblinding becomes necessary after the participant’s withdrawal, the treating investigator will request allocation disclosure from the Clinical Evaluation Center. The reason for withdrawal, the revealed allocation, and the involved personnel will be documented. Full formal unblinding will be done by an independent statistician after trial completion, final follow-up, database lock, and preliminary analysis. Sealed envelopes will be employed, and the unblinding process will be thoroughly documented.

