#### Acupuncture technique

Sterilized disposable stainless steel needles (0.30 mm × 40 mm, Hwato) will be employed. The insertion depth will range from 10 to 25 mm based on anatomical location. A standardized reinforcing-reducing manipulation will be applied, involving uniform lifting, thrusting, and rotating maneuvers at 60–90 cycles per minute for 20–30 s per acupoint to achieve deqi.

Deqi definition: Deqi is defined as a combination of subjective sensations reported by the patient (e.g., soreness, numbness, heaviness, and distension) and the objective sensation of needle grasp felt by the practitioner (34, 35). Needle retention: Needles will remain *in situ* for 30 min.

Treatment schedule: Sessions will be conducted once daily, 5 days per week, for a total of 20 sessions over 4 weeks. Each session will last approximately 40 min.

For rTMS, stimulation will be delivered to the contralateral M1 hand area using the Shenzhen Yingzhi M-50 apparatus. The M1 hand area will be identified using the international 10–20 EEG system for scalp electrode placement, with the target site at C3 (for right hemiparesis) or C4 (for left hemiparesis). The resting motor threshold (RMT) will be determined before the first treatment session to individualize stimulation intensity. Key parameters, including frequency, intensity, and pulse configuration, are summarized in Table 2. The schematic diagram of M1 is shown in Figure 3.

**Table 2 tab2:** Parameters for repetitive rTMS protocol.

Parameter	Specification
Device	Shenzhen Yingzhi liquid-cooled circulating M-50 Ultimale rTMS therapeutic apparatus
Stimulation site	Contralateral primary motor cortex hand area corresponding to the painful limb(M1)
Frequency	10 Hz
Intensity	80–120% of resting motor threshold
Trains per session	20
Pulses per train	1 pulses per train
Train duration	10 s
Inter-train interval	10 s
Total pulses/session	2,000
Session duration	19 min 50 s
Treatment schedule	Once daily for 20 consecutive days

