#### Acupuncture technique

Identical needles (0.30 mm × 40 mm) will be used for acupuncture. The insertion depth, manipulation to achieve deqi, deqi criterion, needle retention time (30 min), and treatment schedule (once daily, 20 sessions) will be standardized to match the procedures in the experimental group, leaving only the acupoint prescription as the major variable.

rTMS procedure:

The rTMS protocol (parameters, site, and schedule) is identical to that described for the experimental group.

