#### Control group 2: sham acupuncture + rTMS

Acupuncture technique:

Acupoint selection: The same set of 12 acupoints used in the experimental group will be used for the control group.

Sham needling technique: The non-penetrating Streitberger-type placebo needle (Asiamed) will be applied at each acupoint (36, 37). This device has a blunt tip that retracts into the handle upon contact with the skin, allowing insertion without piercing the skin. The needle will be fixed in place with an adhesive ring to mimic the appearance of a real needle.

Simulated deqi: To maintain blinding, the acupuncturist will gently manipulate the sham needle handle periodically without applying penetrating pressure and will ask open-ended questions about sensation, not mentioning specific deqi sensations.

Needle retention: The sham needles will remain in place for 30 min, matching the retention time in the active acupuncture groups.

Treatment schedule: The session frequency and duration (once daily, 20 sessions) will be identical to the other groups.

rTMS Procedure:

The rTMS protocol (parameters, site, and schedule) will be identical to that described for the experimental group.

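### The stated basis for blinding, that only the acupoints differ between groups, is untrue for YLDJJ versus sham, where the acupoints are the same and the needle, penetration and manipulation differ

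*Protocol article*

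**What the plan says.** All references are to the protocol article.

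- **Blinding and unblinding procedures.** After noting that the rTMS devices look and sound the same, the section says: "Needles of the same specification (0.30 mm × 40 mm) will be used in the manual acupuncture group". It continues: "Only the acupoints will differ between groups, thereby preserving blinding integrity". It then states: "Participants, outcome assessors, and statisticians will remain blinded to group assignment". It adds uniform rTMS procedures, private rooms for acupuncture and, for practitioners who cannot be blinded, standardised communication scripts.
- **Acupuncture technique (experimental group).** Ordinary steel needles are inserted 10–25 mm and manipulated, "involving uniform lifting, thrusting, and rotating maneuvers at 60–90 cycles per minute for 20–30 s per acupoint to achieve deqi". Deqi combines sensations that the patient reports with the needle grasp that the practitioner feels.
- **Acupuncture technique (control group 1).** Needles, depth, manipulation, deqi criterion, retention and schedule match the experimental group, "leaving only the acupoint prescription as the major variable".
- **Control group 2: sham acupuncture + rTMS.** On the points: "The same set of 12 acupoints used in the experimental group will be used for the control group". The needle is a non-penetrating placebo device. On fixation: "The needle will be fixed in place with an adhesive ring to mimic the appearance of a real needle". The handle is moved gently from time to time, and the acupuncturist "will ask open-ended questions about sensation, not mentioning specific deqi sensations". Retention time, schedule and rTMS match the other arms.
- **Primary outcome analysis.** YLDJJ + rTMS superior to sham + rTMS is the first pre-planned contrast on VAS. The two contrasts together are said to test the specific efficacy of YLDJJ acupuncture.

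**The concern.** The sentence on acupoints gives a reason why blinding holds, and it gives that reason for the groups in general. For the sham contrast it has the facts the wrong way round: the acupoints are what stays the same, and the needling procedure is what changes.

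The VAS score is the participant's own rating. Blinded assessors and statisticians cannot protect it if the participant suspects the allocation. Blinding of participants is therefore the main safeguard when a YLDJJ-versus-sham difference is read as a specific needling effect rather than expectation. The intervention is repeated over 20 sessions, so any cue is repeated as well. A plan that believes only the points differ has no reason to look for such cues or to remove the avoidable ones.

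**Working it through.** No figure in the plan depends on this point, so the check is a comparison of the sections.

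**Step 1. Compare the arms, element by element.**

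| Element | YLDJJ | Conventional | Sham |
|---|---|---|---|
| Acupoints | 12 Yuan-Source and Luo-Connecting points | A different set of 12, mainly around the shoulder | Same 12 as YLDJJ |
| Needle | Steel, 0.30 mm × 40 mm | Identical to YLDJJ | Non-penetrating placebo device |
| Penetration | 10–25 mm | Matched to YLDJJ | None |
| Manipulation | 60–90 cycles/min, 20–30 s per point, aimed at deqi | Matched to YLDJJ | Gentle, periodic; no rate or duration given |
| Adhesive ring | Not mentioned | Not mentioned | Yes |
| How sensation is asked about | Not stated | Not stated | Open-ended, deqi sensations not named |
| Retention | 30 min | 30 min | 30 min |
| Schedule | 20 sessions | 20 sessions | 20 sessions |
| rTMS | Active | Identical | Identical |

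**Step 2. Test the sentence on each pre-planned contrast.**

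- YLDJJ versus conventional: the points differ and the stated needling elements match. The sentence holds.
- YLDJJ versus sham: the points match. Needle, penetration and manipulation differ, and each is stated for both arms. The sentence is false.

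**Step 3. Separate stated differences from silence.** Needle, penetration and manipulation are firm. The ring and the form of questioning are described for sham and simply not mentioned for the real-needle arms. In a condensed article that does not show they are absent there, so these two are open questions.

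**Step 4. Size of the one handling difference that has figures.**

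- Shortest: 12 points × 20 s = 240 s = 4 min per session.
- Longest: 12 points × 30 s = 360 s = 6 min per session.
- Over 20 sessions: 80 to 120 min of active manipulation.

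The sham section gives no corresponding duration.

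**Step 5. Do the other measures cover the sham contrast?**

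- Uniform rTMS: every arm receives the same active rTMS, so it gives no information on the acupuncture arm and cannot hide it either.
- Private rooms: they stop participants seeing other arms. They do not hide what is done to the participant.
- Communication scripts: the sentence that introduces them names practitioners of YLDJJ and conventional acupuncture. Those giving sham are not named.
- Bang's index (Exploratory outcomes, Blinding): it can show that blinding failed, but it neither prevents the failure nor removes the bias.

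**Step 6. Can the bias in VAS points be calculated?** A rough form is bias = (share of sham participants who recognise the sham) × (expectation effect on VAS). The protocol gives neither input, so no figure follows from it.

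**The case against.** **The sentence may be meant only for the two real-needle arms.** The sentence before it speaks of the manual acupuncture group, and the control group 1 section makes the same point for YLDJJ versus conventional. This is a fair reading of the intention. But the wording is about groups without limit, in the section that covers blinding for the whole trial. On the narrow reading the section would offer the sham contrast only the measures in step 5, which do not mask the needling itself.

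**The sham section handles blinding openly.** It uses a placebo needle, says the ring is there to imitate a real needle, and gives maintaining the blind as the purpose of the handling and questions. Retention, schedule and rTMS are matched. All of this stands, and it is why the point concerns a risk.

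**A reader might infer that participants can recognise the sham.** The documents do not establish that. This is a parallel-group trial in private rooms, and a ring or gentler handling is a cue only to someone who knows or guesses what real needling involves.

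**A reader might infer that the ring and questioning differ by design.** That rests on silence. Patient-reported deqi is compatible with open-ended questions, and the real needles may also have a ring.

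**Some of the difference cannot be avoided.** A non-penetrating needle cannot be lifted and thrust in tissue. That is right. It does not apply to when the handle is touched, for how long, or what is said.

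**Conclusion.** The sentence is false for YLDJJ versus sham and should be corrected. That rests only on stated text: the same 12 points, a different device, 10–25 mm insertion against none, and 20–30 s of manipulation per point against gentle, periodic handling. It matters because this is a pre-planned contrast on a self-reported primary outcome, and the reason given for intact blinding does not apply to it.

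The conclusion is limited to an avoidable risk of unblinding. Its likely direction, if realised, is in favour of YLDJJ, assuming that participants who suspect sham expect and report less relief. Its size cannot be derived from the documents, and a share of the 1.5-point clinically meaningful reduction should not be attached to it. The only figure that follows is the 4–6 minutes of active manipulation per session, against no stated duration in sham.

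This does not invalidate the design. It is worth correcting because the stated rationale is wrong for a primary contrast and the remedy is cheap.

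**What to change.** 1. Replace the sentence under Blinding and unblinding procedures with one that says what differs in each contrast: acupoints for YLDJJ versus conventional acupuncture; penetration, and the manipulation that depends on it, for YLDJJ versus sham.
2. In the sham arm, time the handle manipulation to the same moments and the same 20–30 s per point as in the active arms, still without penetration.
3. Mount real and sham needles with the same adhesive ring in all three arms, or state that this is already done.
4. Use one open-ended sensation script in all three arms, with the practitioner judging deqi from the answer and the needle grasp, or state that the script is already common. Say that the communication scripts also bind those who give sham.

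Keep Bang's index as planned, as a check on whether these measures worked.

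The cost is rings for the two active arms, a little more handling time at each of 12 points, one common script and a line in the existing acupuncturist training. Sample size, outcomes and analysis do not change.
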